### Procedure

**
*Obtaining consent.*
** The trial research assistants will be trained by the trial Principal Investigator to obtain informed consent. The research assistant will obtain informed consent at the first observation point, which will normally take place in the home of the participant. After participants express an interest in the study to the ALONE service, the research assistant will provide them with information leaflets and an informed consent form by post (see
*Extended data*;
[name] *et al.*, 2020). Following a period of at least seven days after the information is likely to have been received by the participant, the research assistant will contact the potential participant and at this point, if they are still interested in the study, conduct a short screen (based on the above inclusion and exclusion criteria) by phone. If eligible, the potential participant will then receive a home visit from the research assistant to discuss informed consent and if consenting, to conduct the first observation. Once the research assistant is satisfied that the potential participant has read (or had read to them) and fully understood the information leaflet, they will proceed to obtain written informed consent. The written consent informs participants that they are permitted to withdraw from the study at any time, and they will take their own copy of this consent form and information leaflet, signed by themselves and by the research assistant, from this first meeting. Contact details of the broader research team are available on this leaflet should participants wish to discuss the study or their involvement further.

**
*Participant timeline.*
** The participant timeline is illustrated in the schematic diagram (see
Figure 1). Participants can be enrolled to the study between November 2018 and January 2021. Enrolment involves a washout period of seven days after provision of information leaflets, to allow participants time to consider their potential participation. Enrolment follows a positive eligibility screen, and informed consent is taken at the point of enrolment (t
_1_). The first observation is made at this time point too. This observation includes baseline (non-time varying) covariates. These covariates are age, gender, number of years in education, marital status (responses are single, divorced, separated, married living with spouse, cohabiting with partner, divorced), living status (living alone, living with spouse only, living with child/stepchild/grandchild, living with another relative, living with unrelated individuals). The outcomes and time-varying covariate (social support) listed above are measured at each of the 13 observations. The first observation is made in person while all subsequent observations are made by phone.

**Figure 1. f1:**
[figure not shown]
Schedule of enrolment, interventions, and assessments for HALO study participants.

**
*Data collection and management.*
** Data for the quantitative aspect of the study will be collected at 13 time-points, using a structured assessment form. The baseline assessment is administered during an initial visit to the participant’s home, where informed consent will first be obtained. All subsequent assessments take place by phone, at fortnightly intervals over a period of six months. The measures included in the quantitative assessments are described in detail in the outcomes section above. The project research assistant will collect and manage all quantitative assessment data. A number of measures are in place to promote data quality. Written standard operating procedures are used for data collection and input, including scripts and instructions for administration of all measures. The research assistant is experienced in conducting psychosocial and neuropsychological assessments with older adults, and also received initial training from the senior investigators to ensure competence in administering the specific study measures.

Qualitative data will be collected during a semi-structured dyadic interview with befriendee-befriender pairs (interview guides are available as
*Extended data*;
[name] *et al.*, 2020). These interviews will be conducted by the project research assistants and senior investigators, who are experienced in collecting qualitative interview data. All interviews will be audio recorded using a digital recording device.

Since data collection takes place every two weeks, the research assistant will be in regular telephone contact with research participants. To promote retention, phone assessments will be scheduled for a regular time/day that the participant has identified as being convenient. In the case of a missed observation, the research assistant will make multiple follow-up contacts in an attempt to complete the assessment. The statistical modelling techniques being used can accommodate incomplete data, therefore continued engagement will be encouraged even if an observation is missed. If a participant is overly taxed with their engagement in the study, research assistants will suggest that they participate at least in the final time point (after 26 weeks).

Quantitative data is initially collected using written assessment booklets. Data from these booklets are then entered into an electronic file for further processing and analysis. Quantitative data entry is conducted by the project research assistant. Data entry and initial processing is conducted using Microsoft Excel; an Excel-based data entry system was developed that includes automated processes designed to reduce human error during data entry and processing. These include instructive prompts, automated range checks for all values and automated calculation of total/scale scores etc. Ongoing data audit procedures are also used by research team members not including the project PI to ensure data quality, including cross-checking of scoring and data entry by a second member of the study team for a random sample (10%) of cases.

Qualitative interview data is recorded using a digital recording device. All audio recordings will be transferred to a secure PC system immediately after interviews and then deleted from the digital recording device. These audio recordings will then be transcribed verbatim for analysis. Transcripts will be checked against audio recordings to ensure data quality.

All research data in both written and electronic records are stored under a unique participant ID code, and no identifying information is included in either written or electronic data files. Written assessment booklets are stored securely in a locked filing cabinet within a locked office at the host institution. All electronic data files (quantitative data file, qualitative audio recordings and transcripts) are password-encrypted and stored on a password-protected, secure PC system within locked offices at the host institution. Access to these files is limited to members of the research team. All data management procedures have been approved by the relevant Research Ethics Committee within the host institution. A Data Protection Impact Assessment (DPIA) was also submitted and approved by the Data Protection Office within the host institution. Should any protocol amendments be required throughout the duration of the study, the PI will take responsibility to inform the research ethics committee (and apply for ethical approval afresh, if required), the funder, ClinicalTrials.gov, journals, collaborators, and trial participants if necessary. The named collaborators (authors of this protocol) will have access to the final dataset.

**
*Confidentiality.*
** To maintain confidentiality, all participants are assigned a unique study ID code. All study data is collected and stored under this ID code, separate from personal identifying information. ALONE will provide the research team with contact details (name and phone number) for potential participants, subject to the consent of the participant for that information sharing. At this point a study ID code will be assigned to the potential participant. The research assistant will maintain a ‘key’ file which will link the participant’s study ID code to their name and personal contact information. Further contact information such as addresses for home visits will be collected by the research assistant at study enrolment, and added to this ‘key’ file. This electronic, password-encrypted file will be stored on a password-encrypted, secure PC system. Access to this file will be limited to the research team, and will be used only to arrange home visits, or to allow the research team to withdraw data from the study if requested. Participants provide informed consent for the processing and storage of their personal data as outlined above.

### Analytic plan

In order to test hypothesis 1, that befriending services will lead to a positive change in health-related quality of life and brain health, two separate generalised additive models will be performed. Data are longitudinal, with 13 time points at which they are collected, before and after a befriending match has been made. The data analysis protocol for the quantitative component of the study is as follows: first, after data collection and audit, visual inspection of plotted data at the individual and group level will be done for both outcomes of interest. Next, pre-intervention and post-intervention trends will be inspected, as well as mean shifts, slope changes, and variability across participants. With respect to verbal fluency as an outcome, data will be analysed for practice effects using published guidelines (
Vivot *et al.*, 2016) and if practice effects are detected, this should be specified in the final model. The modelling of these practice effects is itself of interest and can inform future research attempting to conduct repeated cognitive measures. If practice effects are considerable, this could represent a risk for the interpretability of the results, but since the cognitive outcome is a secondary measure in the study design, this risk does not affect the overall study feasibility. Inferential analyses will be conducted using a generalised additive model (GAM) (
Shadish *et al.*, 2014b) based on a multilevel approach where time points are nested within participants (
Shadish *et al.*, 2014b). This approach is semi-parametric, and calculates autocorrelations from extracted residuals. Time will be scaled such that point 0 is the end of the baseline (two time points of data collection will be conducted during baseline). The GAM approach improves on some key limitations of the multilevel approach, since with the latter, the functional form of the trend must be known, whereas in the former, a smoothing function can be used to model the trend in the data. The moderation effect (investigating whether befriending moderates the impact of loneliness on health and cognitive function) is modelled as an interaction term: the product of the two predictors (loneliness and befriending phase, operationalised as 0 indicating pre-intervention, and 1 indicating post-intervention). This modelling approach will be deployed using the mgcv package in R Studio software (
Wood, 2011).

The GAM approach is relatively robust to missing data, and imputation can be incorporated into the analysis. An additional advantage of the GAM approach is that equal numbers of data points per participant is not a requirement.

Statistical code will be published with any publication to arise from the study. Participant level data will not be archived, but we hope to make available a covariance matrix arising from the data, which can be shared upon reasonable email request.

The next step in the analysis plan concerns the qualitative data. The qualitative interview data will be analysed according to principles of constructivist grounded theory (
Charmaz, 2006) in three parts: befriender interviews, befriendee interviews, and dyadic interviews. Existing findings about potential mechanisms through which befriending may impact health will serve as sensitising concepts in these interviews. Themes arising from all three types of interview will be integrated and compared as per existing guidelines (
Eisikovits & Koren, 2010). Finally, a mixed methods triangulation protocol will finally be conducted to integrate the qualitative and quantitative findings (
Tonkin-Crane *et al.*, 2016).

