### Sample

Quantitative component: Sample size was calculated to ensure that the study was sufficiently powered. Power in single-case experimental designs is a function of the following: sample size (number of observations per phase multiplied by number of participants), intraclass correlation (ratio of between-case variance to total, or within and between case variance), auto-correlation, effect size to be detected, and the nominal Type 1 error rate (
Shadish *et al.*, 2014a). A rigorous approach described by
Shadish and colleagues (2014a) to calculating sample size uses the alternative d-statistic to the traditional statistic used in between-subjects designs for single case designs. Our primary outcome of interest is health-related quality of life, which will be measured using the EQ-5D scale (see Outcomes). The minimally important difference in this scale has previously been calculated as 0.074 (
Walters & Brazier, 2005) and norms of the EQ-5D have yielded a standard deviation of 0.23 (
Kind *et al.*, 1999). These figures were used to estimate an effect size (using Shadish’s alternative d-statistic) of 0.32. Using this figure in a simulation macro provided by
Shadish and colleagues (2014a), with intraclass correlation set to a conservative estimate of 0.5, autocorrelation set to same, and alpha set to 0.05 for a multiple baseline design) with 13 observations (i.e. a period of six months, specified to be at least two observations in “A” phase, and the rest in “B” phase) per participant, and desired power of 0.8, a sample size of 85 is required. This sample size also provides sufficient power (0.9) for the secondary outcome (brain health), calculated using the same approach described above.

Qualitative component: 10–15 befriendee-befriender pairs will be recruited via the collaborating organisation. Sample size estimation in constructivist grounded theory is guided by data review after 3–4 interviews are conducted to assess thematic saturation (
Charmaz, 2006).

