
Receipt of the befriending service intervention is at the discretion of the service user. They are permitted to withdraw from the service at any time if they wish, or request an alternative befriending partner. Should participants withdraw from the befriending service they will be invited to continue with data collection since this will facilitate the examination of ABA (no intervention, intervention, no intervention) phased analysis of the trajectories of outcomes (on an individual basis, with trends rather than inferential statistics being the focus). After completion of the study data collection, it is anticipated that participants will continue to receive the intervention indefinitely, at their discretion.

For the purpose of this study, participants are their own comparators. The reason for this is that the service under investigation is already running in the community and desirable to potential participants. As such it would be unethical to create a control arm as a comparator since these participants would then fail to receive the befriending service that they have requested in good time. The study design permits the research team to measure study outcomes before and after the intervention (befriending service) commences delivery, for a six-month period. As a result, participant outcomes after commencement of the intervention can be compared to those outcomes before this event.

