### Outcomes

**
*Primary outcome: Changes in health-related quality of life over six months.*
** EuroQOL (quality of life) five-dimension scale with five response levels (EQ5D-5L) (
Rabin *et al.*, 2014). This scale is a well-validated scale of health-related quality of life, measuring five dimensions of health: mobility, self-care, usual activities, pain, and anxiety/depression. The score is suitable for repeated measures and yields scores of five levels of severity for each dimension. Scores can then be combined into a single summary index of utility. A score of 0 on the EQ5D indicates death, while a score of 1 indicates perfect health. The EQ5D-5L is administered at each of 13 observations made two weeks apart for a minimum of two observations before the intervention begins and a maximum of 11 observations after.

**
*Secondary outcome: Changes in brain health over six months.*
** Measurement and definition issues remain in the study of brain health, but most studies exploring this concept rely on either global or domain specific measures of cognitive function which are known to decline in later life, such as memory and executive function (
Wang *et al.*, 2020). Repeated testing of cognitive functioning can result in practice effects, and two strategies are put in place to minimise these. First, specific analytic strategies will be used to detect and account for practice effects in the data. Second, tasks are chosen to minimise the effects of practice on outcomes (
Goldberg *et al.*, 2015). Two alternating versions of the verbal fluency task from the Delis Kaplan Executive Functioning System or DKEFS (
Delis *et al.*, 2001) are available for this purpose, and will be used alternately at observations across 13 timepoints. The DKEFS is a standardised set of executive function tests designed for use across the lifespan. There are nine test in the DKEFS, including the trail making test, the tower of Hanoi test, and the colour-word interference test. Tests from the DKEFS can be used alone, and the verbal fluency task was chosen, because as well as measuring an aspect of brain health (
Wang *et al.*, 2020), as it is a well standardised measure which incorporates an alternate version so that practice effects can be reduced (of key concern in a study design with 13 observations).

**
*Time-varying moderator: Change in loneliness over six months (13 observations).*

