## Discussion

This protocol describes the pragmatic, embedded evaluation of an existing service which claims to reduce loneliness and mitigate the impact of loneliness on health outcomes for older adults. Currently we are recruiting during the COVID-19 pandemic in which, nationally, older adults are among those being advised to “cocoon” and remain in the home, potentially leading to increased risks of loneliness and social isolation, and higher country-level demands for services to resolve such issues. Inevitably, recruitment has slowed down because fewer services are available to older adults, but recruitment is beginning to recover (June 2020). All data collection and recruitment procedures are, for the time being, conducted by phone to avoid face-to-face visits yielding increased risk of COVID-19 transmission to older adults. Since our sample are at risk of social isolation, it is possible that the data collection process itself will constitute social engagement, and we will reflect on this during the data collection process. It is hoped that the completion of our study will add to the evidence base for the uptake of befriending services for older adults at risk of, or experiencing, loneliness and social isolation.

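### A 0/1 befriending phase beside a smooth on time centred at the end of baseline can detect an abrupt shift but almost no gradually building benefit, and the centring discards any stagger in waits

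*Protocol article*

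**What the plan says.** All references are to the protocol article.

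- **Time axis** (Analytic plan): "Time will be scaled such that point 0 is the end of the baseline", followed in brackets by "two time points of data collection will be conducted during baseline".
- **Trend** (Analytic plan): "a smoothing function can be used to model the trend in the data".
- **Phase** (Analytic plan, in the sentence on moderation): "operationalised as 0 indicating pre-intervention, and 1 indicating post-intervention". Slope changes appear only among the features to be inspected before modelling. No slope-by-phase or time-since-start term is stated for the inferential model.
- **Length of baseline**: Sample says "specified to be at least two observations in" the A phase and names a multiple baseline design. Outcomes says "for a minimum of two observations before the intervention begins and a maximum of 11 observations after".
- **Start of the B phase**: Analytic plan describes data before and after a match. Intervention compares outcomes "before and after the intervention (befriending service) commences delivery" and places the first accompanied visit after the match.
- **Other influences running from enrolment**: Discussion accepts that "it is possible that the data collection process itself will constitute social engagement", and Analytic plan expects possible practice effects on verbal fluency.

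**The concern.** On an axis centred at the end of each participant's baseline, phase equals 1 exactly when time is above 0, for everyone. The phase coefficient therefore measures only a jump at that point, and any smooth rise afterwards is available to the smooth. Befriending is a weekly visit and the primary outcome is change over six months, so a benefit that accumulates is a natural form for the effect to take. The trial could reach the full minimally important difference by the end of follow-up and still report no effect on hypothesis 1.

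Secondly, a multiple baseline design gains strength from participants starting at different times after enrolment. Centring every clock at the end of baseline removes that difference from the model. With it goes the information that helps distinguish befriending from practice, fortnightly contact and natural recovery, all of which run from enrolment.

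**Working it through.** **Inputs.** From Sample: 85 participants, 13 observations, intraclass correlation 0.5, autocorrelation 0.5, difference 0.074, SD 0.23. From Analytic plan: two baseline observations, so a 2 + 11 split. My assumptions: shapes of benefit and trend, number of spline terms, and, where waits vary, equal numbers waiting 2, 3, 4, 5 and 6 observations.

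**Plan's own figures.** 0.074 / 0.23 = 0.32, which reproduces the stated effect size. It is a difference in means over an SD, that is, a constant shift. The sample size of 85 comes from a simulation macro not in the document. A generalised least squares (GLS) phase contrast without trend needs about 27, but that is a different method, so 85 is not called wrong. Nothing below depends on it.

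**Model.** GLS with covariance V = 0.5 J + 0.5 AR(1; 0.5), where J is a matrix of ones. The design is trend + phase. Expected coefficient = (ΣX′V⁻¹X)⁻¹ ΣX′V⁻¹μ. Power = Φ(0.32/SE − 1.96). SEs are in SD units.

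**Step 1: all baselines of two observations.** The benefit rises linearly to 1 over the 11 B observations, so its true B-phase mean is 0.545.

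| Trend term | Phase coefficient for the gradual benefit | SE of a step | Power for an abrupt 0.32 |
|---|---|---|---|
| none | 0.36 | 0.063 | >0.99 |
| linear | −0.02 | 0.075 | 0.99 |
| quadratic | 0.01 | 0.092 | 0.94 |
| 4-df cubic spline | 0.05 | 0.101 | 0.89 |

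An unpenalised spline with eight basis functions lowers the step power to 0.52.

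**Step 2: penalised smooth.** 300 simulated trials per scenario; REML-penalised cubic spline, basis dimension 10, plus phase; covariance as above, baselines of two.
- Abrupt 0.32: estimate 0.32, rejection 0.98.
- 0.32 built over 11 observations: estimate −0.003, rejection 0.06.
- 0.32 built over 6 observations: estimate 0.03, rejection 0.05.
- No effect, with flat, linear or early-rising trend: rejection 0.04 to 0.07.

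A gradual benefit is thus rejected at about the nominal error rate.

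**Step 3: is the axis the cause?** If every baseline has two observations, centring only shifts the origin and the GLS results on the two axes are identical. With waits of 2–6 and phase alone, a 0.32 benefit built over 11 observations gives 0.01 (rejection 0.07) on the centred axis and 0.02 (0.06) on the enrolment axis. Changing the axis alone does not recover it.

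**Step 4: axis plus a time-since-start term.** Waits 2–6, 4-df trend.

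| | Centred axis | Enrolment axis |
|---|---|---|
| SE of step (phase only) | 0.097 (power 0.91) | 0.087 (power 0.96) |
| SE of effect 10 weeks after start (phase + slope) | 0.54 | 0.22 |
| Share of an enrolment-driven recovery (time constant 3 observations) credited to befriending at 10 weeks | −0.21 | 0.00 |

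Power after the change: if 0.32 is already reached at 10 weeks, 0.32/0.22 = 1.45 and Φ(1.45 − 1.96) = 0.31. If it builds over 11 observations, the 10-week effect is 0.32 × 5/11 = 0.145, and Φ(0.145/0.22 − 1.96) = 0.10. The simulated joint test of phase and slope rejects in 0.12 (built over 11 observations) to 0.17 (over 6).

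**The case against.** A step beside a smooth is the ordinary interrupted-time-series model, and it is identified. A reader might infer that the model cannot separate befriending from elapsed time at all. That is not supported: an abrupt 0.32 is recovered without bias, and its power stays above the planned 0.80 with trends of up to 4 df. The condition is that the underlying trend is smooth and nothing else jumps at the start.

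A reader might also blame the choice of time zero for the whole problem. Step 3 of the check shows otherwise. The step-only phase, the short baseline and the lack of a concurrent control do most of the damage, and Intervention openly adopts the last of these on ethical grounds.

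A third tempting reading is that the boundary is fixed at the second observation, so that longer waiters' later baseline observations are coded as post-intervention. The coding sentence defines phase by intervention status, not observation number, and that reading is incompatible with centring at each participant's own baseline end. What remains is a wording conflict between two and at least two observations. The match-versus-visit difference cannot be sized, because no gap between them is given.

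It is fair, too, that the article gives no full model formula. A slope-by-phase term is not excluded, and the basis dimension may properly sit in a fuller plan. But the time axis, the 0/1 coding and the inspection-only role of slope changes are stated here. Random individual trends, mentioned under Outcomes, do not supply a slope change at the start of befriending.

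Finally, the repair is limited: power for a gradual benefit stays low, and waits depend on preferences and location.

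**Conclusion.** The point holds in a limited form. As described, the test of hypothesis 1 is sensitive to an abrupt shift and nearly blind to a benefit that builds: the phase coefficient is −0.02 to 0.05 of the final effect for a linear rise over the B phase, and about a tenth (0.03 of 0.32) for a rise over six observations with a penalised smooth. Where waits vary, centring gives up a modest gain for a step (SE 0.097 against 0.087) and a large one for an effect at a stated time (0.54 against 0.22). The stated 80% power should be read as power for an abrupt mean shift.

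This rests on a single smooth with a 0/1 phase, as the article describes, on the plan's correlation inputs, and on assumed benefit shapes and waits. The document gives no distribution of waits. If nearly all participants wait exactly two observations, the stagger is absent and the second part of the point falls away; the first does not.

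**What to change.** Before analysis, change the wording of the Analytic plan as follows.

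1. Fit the smooth on time since enrolment.
2. Code phase from each participant's own start of befriending.
3. Add a time-since-start (slope-change) term, and name the modelled effect at a stated time as the hypothesis 1 estimand.
4. Reconcile two with at least two baseline observations, and the match date with the start of the service, across Sample, Intervention, Outcomes and Analytic plan.
5. State that the 80% power refers to an abrupt mean shift, and that power for a gradual benefit is about 0.3 or less even with waits of 2–6 observations (an assumed range).

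Dropping the smooth is not a remedy: with phase alone and baselines of two, about half (0.51) of a recovery running from enrolment with a time constant of 3 observations would be credited to befriending.

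The cost is analysis wording, plus obtaining start dates from the service. The downsides should be stated. The gain depends on waits varying, and waits are not randomised. The smooth must also be flexible enough: with a steep early rise (time constant one observation, assumed), no benefit and waits of 2–6, the simulated joint test falsely rejected in 0.12 on the enrolment axis and 0.19 on the centred axis.
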